### Participants

The study will be solely undertaken at St Vincent’s Public Hospital. The care providers involved with the study will include plastics and reconstructive surgery consultants and registrars. A total of 500 patients will be recruited and divided evenly into the two treatment groups.

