### Inclusion and Exclusion Criteria

Inclusion criteria for the study include (1) greater than or equal to 18 years of age; (2) able to give informed consent and willingness to participate in follow-up; and (3) undergoing any plastic surgery procedure involving excision of skin lesions. Exclusion criteria include those requiring re-excision through the original wound and undergoing injectable corticosteroid therapy into the scar.

The patients will be randomly allocated to receive either the deckled incision or the straight line incision for their surgery. In patients with multiple (two or more) separate lesions requiring separate incisions, each lesion will be randomly allocated to receive either the deckled or straight line incision. Only the treating surgeon will be aware of which incision was used and the patient will be blinded to the type of incision. The surgeon will document in the operation note the number and site of lesions, whether they were deckled or not, the precise length of the scar, and whether the procedure was carried out by a registrar or consultant.

The patient will be followed-up in the outpatient clinic. Standard post-operative care with micropore tape will be given to both groups with respect to scar minimization. The scar and compliance with standard post-operative scar reduction will be assessed at 1 week, 3 months, and 6 months post-operatively using the POSAS [5]. The 6-month cut off was chosen as scars have usually matured by 6 months to reflect their final life-long appearance and to avoid a large number of patient attrition over a longer follow-up period (Figure 1).

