### Investigation Plan

The intervention plan is shown in Table 1.

**Table 1 table1:** Intervention plan.

List interventions	Enrolment visit	1 Week	3 Months	6 Months
Informed consent	✓			
Inclusion/exclusion criteria	✓			
Medical history	✓			
Patient and observer scar assessment scale (POSAS)		✓	✓	✓
Adverse event and serious adverse event assessment		✓	✓	✓

The follow-up will be done in the outpatient setting. The POSAS requires at least three independent assessors to achieve a valid result and this will be done by a combination of medical and nursing staff. The results will be recorded in real-time on a tablet (iPAD), which has been pre-populated with the patient demographics and the unique study code identifier that can be cross referenced with the medical records. The data is automatically backed up to an online database via Dropbox. Selected photographs will be taken by a digital camera for future publication purposes.

The routine standard of follow-up will vary with each individual procedure and thus the above protocol is not the standard of care. The additional costs of the procedure will be covered by the Plastics and Reconstructive Surgery Department.

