### Statistical Consideration

Sample size was calculated on the basis of a type I error of 5% (ie, *P* <.05) and a type II error of 10% (ie, power of 90%) with the aid of a statistician. Using formal sample size calculations we estimated a sample size of 250 patients for each treatment group. We anticipate an attrition rate of 10%, and subsequently, have increased our sample size by that amount for each treatment group.

Statistical analysis will be carried out by an external statistician. We intend to use independent two-sample *t* tests on primary endpoints and both chi-squared and independent two-sample *t* tests on secondary endpoints.

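### A two-sample t test on a score taken three times, with 10% attrition expected, cannot use earlier scores for scars not seen at 6 months; a repeated-measures model can

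*Protocol article*

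**What the plan says.** All references are to the protocol article.

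- **Objectives.** The primary endpoints are the observer and patient components of POSAS. No visit is attached to either.
- **Inclusion and Exclusion Criteria; Investigation Plan, Table 1.** POSAS is scored at 1 week, 3 months and 6 months. Ending at 6 months is justified by scar maturity and by the wish "to avoid a large number of patient attrition over a longer follow-up period". Separate lesions in one patient are randomised separately.
- **Statistical Consideration.** On the primary analysis: "We intend to use independent two-sample *t* tests on primary endpoints". On losses: "We anticipate an attrition rate of 10" per cent, with the sample size said to be increased accordingly. On size: "we estimated a sample size of 250 patients for each treatment group", at 5% type I error and 90% power.
- **Participants.** "A total of 500 patients will be recruited and divided evenly into the two treatment groups".
- **Enrolment Procedure.** The final analysis is to be stratified and adjusted for recorded baseline characteristics, with special interest in earlier radiotherapy and lesion site.

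**The concern.** The trial measures each scar up to three times and expects to lose about 50 of 500 patients (10% of 500). The test named for the primary endpoints compares two sets of single values. If it is applied at 6 months, the visit that the article's own reasoning favours, it cannot use the 1-week or 3-month score of a scar that is missing at 6 months.

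Two things are at stake. The first is precision: earlier scores on the same scar say something about the missing one. The second is bias. Patients may return for a scar check partly because of how the scar looks or feels, and the Investigation Plan says that this follow-up is not the standard of care. If return depends on the earlier score, and does so differently in the two arms, the scars seen at 6 months are no longer a fair comparison. Enrolling more patients can restore precision but does nothing about that bias.

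**Working it through.** **Inputs from the article.** Type I error 5% (two-sided assumed, as sidedness is not stated); power 90%; 250 per arm; 1:1 allocation; attrition 10%.

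**Assumptions, not in the article.** Correlation r between 3-month and 6-month scores, varied from 0.3 to 0.9; all 3-month scores observed; one scar per patient; dropout mechanisms as described in step 4.

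**1. The plan's own figure.** No effect size or SD is given, so 250 cannot be reproduced. Only the standardised difference that it implies can be back-calculated:

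d = (1.96 + 1.2816) × √(2/n)

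- 250 evaluable per arm: d = 0.290 SD
- 225 evaluable per arm: d = 0.306 SD

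Both readings are carried forward. Recruiting 500 in total means 250 per arm randomised and 250 × 0.9 = 225 seen at 6 months. It is not clear whether 250 is the number before or after the attrition allowance.

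**2. Power of the t test with 225 per arm.** Power = Φ(d × √(n/2) − 1.96).

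- 250 is the number before attrition (d = 0.290): 86.8%
- 250 already includes the allowance (d = 0.306): 90.0%

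**3. Power when earlier scores are used.** With 6-month scores on 225 and 3-month scores on 250, the effective number per arm is

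n_eff = 1 / [(1 − r²)/225 + r²/250]

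For r = 0.6: 1 / (0.64/225 + 0.36/250) = 1 / (0.002844 + 0.001440) = 233. With d = 0.290, power is Φ(0.290 × √(233/2) − 1.96), about 87.9%.

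| r | n_eff | Power, d = 0.290 | Power, d = 0.306 |
|---|---|---|---|
| t test only | 225 | 86.8% | 90.0% |
| 0.3 | 227.0 | 87.1% | 90.3% |
| 0.5 | 230.8 | 87.6% | 90.7% |
| 0.7 | 236.6 | 88.4% | 91.4% |
| 0.9 | 244.8 | 89.4% | 92.2% |

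The gain is 0.3 to 2.6 percentage points.

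**4. Bias of the comparison among scars seen at 6 months.** Simulation with 2,000,000 scars per arm, no true difference, and 10% dropout in each arm. Where dropout depends on the 3-month score, it follows a logistic rule with log-odds 1 per SD. Absolute bias in SD units:

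| Dropout depends on the 3-month score | r = 0.5 | r = 0.7 |
|---|---|---|
| Same way in both arms | about 0 | about 0 |
| In one arm only | 0.046 | 0.063 |
| In opposite directions | 0.090 | 0.127 |

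The bias is close to proportional to r (0.046/0.5 = 0.092; 0.063/0.7 = 0.090), so at r = 0.6 it is about 0.055 SD for one arm only and 0.11 SD for opposite directions. The standard error of the 6-month difference is √(2/225) = 0.094 SD. These are therefore about 0.6 and 1.2 standard errors, or 19% and 38% of the 0.290 SD difference (0.055/0.290; 0.11/0.290).

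An estimate using the 3-month scores had bias of at most 0.001 SD in every case. That is expected, because the simulated dropout depends only on a score that the estimate uses.

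**The case against.** A reader might infer that the plan fixes a completers-only t test at 6 months and throws the earlier scores away. The article does not say this. It names no primary visit, states no complete-case rule, and words the t test as an intention. T tests at each visit would use the 1-week and 3-month scores, though for different questions, and imputation before a t test is not excluded. Silence on missing data is no fault in an article whose analysis plan is not shown. What stands is narrower: the test that is named has no means of its own to carry earlier scores into the 6-month comparison.

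The t test is also not the only analysis mentioned, since Enrolment Procedure promises a stratified and adjusted one. That is correct, but a plain t test cannot deliver it. A regression-type model is needed in any case, and extending it to repeated measures adds little work.

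On power, the article says that the sample was enlarged for attrition. If 250 already contains that allowance, there is no shortfall. This objection holds, and it means that 86.8% cannot be quoted without its condition.

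On bias, nothing in the article shows that dropout would differ by arm, and patients and outcome adjudicators are to be blinded. The figures rest on assumed mechanisms, and the opposite-direction case is an extreme one. The repeated-measures model is also not protected if return depends on the unseen 6-month appearance. All of this stands. It limits the claim to a risk that is cheap to reduce.

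Finally, a reader might take the statement "The POSAS requires at least three independent assessors to achieve a valid result" as a second route to missing observer scores that the t test cannot handle. The article plans no visits with fewer assessors and does not say how such scores would be treated. The requirement is a scoring rule and applies equally to any analysis, so it is no part of this point.

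**Conclusion.** The point holds as a choice of method that can be improved, not as a demonstrated bias or loss of power. For a score collected three times with 10% expected attrition, the named t test makes less use of the data than a repeated-measures model would at the visit that the article's reasoning favours.

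The precision at stake is small: about one percentage point of power at r = 0.6, and no shortfall from 90% if 250 already includes attrition. The main benefit is protection against bias if dropout depends on earlier scores differently by arm. The correlations, the dropout rules and the treatment of scars as one per patient are assumptions. Taking 6 months as the primary visit is an inference from the reason given for ending follow-up there.

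**What to change.** 1. Name 6 months as the primary visit for both POSAS components.
2. For each component, replace the two-sample t test with a repeated-measures mixed model on all available visits. Include arm, visit, arm by visit, and the baseline covariates promised in Enrolment Procedure. Allow correlation between visits within a scar, and add a random effect for patient because lesions in one patient are randomised separately. Report the arm difference at 6 months.
3. Add a sensitivity analysis in which dropout depends on the unseen 6-month score, for example by shifting the missing scores by a range of amounts that may differ by arm.

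**Cost.** A change of analysis wording and slightly more modelling; no new data, visits or patients. The model assumes that scores are missing at random given the earlier scores and covariates. This is weaker than what a comparison of attenders alone needs, but it is still an assumption, which is why step 3 belongs with the change.

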### Confidentiality, Storage and Archiving

The patients will be allocated a study code and their data will be de-identified. Following completion of the study the data will be kept on a secure server for a minimum of 15 years in the Department of Plastics and Reconstructive Surgery.

## Results

The study is expected to begin enrolment in August 2016. We anticipate that deckling will have superior scar outcomes when compared to the straight line incisions. From clinical experience this is especially true for lesions involving the face and in those areas of the skin that have undergone radiation therapy.

The study will be funded by the Plastics and Reconstructive Surgery Department at St Vincent’s Hospital, Sydney, Australia. Ethics approval has been obtained for the study.

## Discussion

The deckling study is a novel method for improving post-operative scar outcomes. Although this study mainly evaluates scar outcomes following excision of smaller lesions in plastic surgery procedures, its results can be applicable to a broad range of surgical procedures involving the skin. The learning curve associated with a new surgical procedure or technique can limit its uptake by surgeons. The deckling incision is simple to master with a minimal learning curve and has a small impact on the overall operating time.

### Conclusion

The deckling incision is a unique, simple and cost effective technique for improving post-operative scar outcomes.

## Abbreviations

POSAS: Patient and Observer Scar Assessment Scale
RCT: randomized controlled trial

## Appendix

Multimedia Appendix 1 Patient and Observer Scar scale - Observer.

Multimedia Appendix 2 Patient and Observer Scar Scale - Patient.
